### Study design

A multicenter observational case-control study will be conducted at 50 centers from all major geographic regions in the country to account for ethnical, cultural, and socioeconomic aspects.

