### Eligibility criteria

Cases: All participants aged ≥18 years who are hospitalized due to the first occurrence of an acute myocardial infarction (AMI), stroke, or peripheral artery thrombotic event, presenting in the first 7 days from symptom onset will be screened (S3 File).

Eligible cases must have signs and/or symptoms compatible with the acute manifestation of ASCVD. Case definitions include diagnostic criteria based on national and international guidelines. Acute myocardial infarction is defined as: clinical presentation, electrocardiogram patterns (new pathological Q waves, and/or ST-segment elevation of 1 mm in ≥ 2 contiguous leads, or 2 mm from V1 to V3, or new left bundle branch block, or new changes in the ST-T segment, and cTnI or cTnT curve compatible with acute myocardial injury of ischemic nature (which is currently named a type 1 acute MI). Stroke is defined as clinical signs of rapid development of focal or global brain function disorder, lasting more than 24 hours, with no apparent cause other than that of vascular origin (does not include trauma, cancer, infection of the central nervous system), and Computed Tomography or Magnetic Ressonance Imaging with positive results. Peripheral artery thrombotic event is defined as clinical presentation (pain, burning sensation, absence of pulse, decreased local temperature, changes in color) and diagnostic tests (Doppler ultrasound, angiotomography, or arteriography) that show interruption of flow to the lower limbs acutely, of embolic or thrombotic cause, leading to distal ischemia [20–23].

Controls: All participants aged ≥18 years seeking medical care for non-ASCVD conditions will be screened and enrolled during hospitalization; and healthy individuals with no clinical complain will also be screened and enrolled at the same community. Cases and controls will be recruited in a 1:1 ratio adjusted for sex and age.

Exclusion criteria for both cases and controls are previously known ASCVD, e.g., chronic coronary artery disease, stable angina, previous myocardial infarction, percutaneous revascularization procedures (coronary, cerebrovascular, or peripheral), surgical revascularization procedures in any arterial vascular bed, transient ischemic attack, stroke, aortic aneurysm, intermittent claudication, peripheral artery disease that led to amputation.

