### Variables

The exposure to modifiable risk factors in combination with genomic data (polygenic risk score) in both cases and controls will be expressed as odds ratios (95% CI). Multiple logistic regression models will be built to adjust and determine the strength of association between demographic variables (sex, age, race), traditional risk factors (smoking, diabetes, hypertension, obesity, anxiety and depression, unhealthy diet, physical inactivity, alcohol consumption, and apolipoprotein B/A1 ratio [ApoB/ApoA1], and genetic data [PRS]. For each variable with a higher chance of CVD (significant OR), attributable risk estimate will be calculated for the genetic component (PRS) and other covariables. Fig 2 shows the Polygenic Risk Score flowchart.

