### Data analysis

#### Quantitative variables and statistical analysis

The Hardy-Weinberg genetic equilibrium test will be evaluated in the control group using the chi-square test or Fisher’s exact test. To estimate the association between genetic polymorphisms and risk of CVD, univariate and multiple unconditional logistic regression analyses will be conducted [32–36].

Initially, univariate binary logistic regression analyses will be performed. Thus, covariates with a p-value < 0.20 in univariate regression analyses will be considered in multiple logistic regression analysis with selection of variables according to the backward elimination technique [37, 38]. The selection process in the backward elimination allows the sample size to adjust and always uses the maximum available sample as the number of variables in the model drops [37]. Occasionally, covariates judged as confounding factors by the investigator may be forced into the final backward regression model.

Additional multiple logistic regression analyses may also be conducted using a variant of the Purposeful Selection algorithm described by Bursac *et al*. [38].

The assumption of linearity on the logit scale (log-odds) between each quantitative covariate and the binary response variable in binary logistic regression analysis will be evaluated with the construction of “Smoothed Scatter Plots” and the method of fractional polynomials [35–39]. When the assumption is not satisfied, quantitative covariates will be categorized for use in logistic regression using cut-off points, according to the literature, distribution tertiles or optimal cut-off obtained from the Receiver Operating Characteristic (ROC) curve, whichever is deemed most appropriate. In case of an optimal cut-off point, it will be defined as the one that maximizes the Youden index [39, 40].

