Studies have shown that genetic background may exert a significant effect on increased risk of cardiovascular disease [54]. In a mixed population such as ours, determining the attributable risk may lead to the development of actions aimed at specific subpopulations, such as providing appropriate genetic advice and prevention strategies. This is particularly important considering that lifestyle changes and even correct adherence to pharmacological therapies are not implemented or followed in a sustained way.

The contribution of the genetic component on the pattern or susceptibility to diseases in the Brazilian population has already been shown to have an impact on the control and treatment of infectious, autoimmune, and hematological diseases, drug pharmacokinetics, and even on the transplant allocation system [13, 14, 19, 55, 56].

It is worth to cite the potential impact of epigenetics to the pathogenesis of human diseases [57–59]. Currently, the role of control of gene expression by non-coding RNAs is a hot topic of research including cardiovascular diseases [60–62]. Nevertheless, our study aims to assess the association of genomics with ASCVD risk and its impact on the occurrence of acute myocardial infarction, stroke, or peripheral artery thrombotic-ischemic events at population level. Epigenetics studies may be warranted and of interest for future research and study protocols.

The CV-GENES study has some potential limitations. First, since Brazil is a large country with different demographic densities and socioeconomic disparities, assuring equality of individuals allocation based on geographic parameters is challenging. Second, the gold standard genetic test for this purpose is whole genomic sequencing with high cover and depth. Facing the size of our cohort and limited financial support, we decided to combine the whole exome sequencing with low-pass whole genome sequencing to allow for PRS calculation, a successful strategy used by previous studies and supported by guidelines [26, 27, 63, 64].

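### Neither the 1:1 recruitment rule nor the stated model ties cases to controls by centre or region, so ORs and PARs can be confounded by place if site yields differ

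*Protocol article*

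**What the plan says.** All references are to the protocol article.

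- **Study design** places recruitment at "50 centers from all major geographic regions in the country to account for ethnical, cultural, and socioeconomic aspects".
- **Eligibility criteria** sets the balance: "Cases and controls will be recruited in a 1:1 ratio adjusted for sex and age". Patient controls are enrolled during a hospital stay, and "healthy individuals with no clinical complain will also be screened and enrolled at the same community". No number of controls per case is given for a centre or region.
- **Variables** lists the covariates, beginning with "demographic variables (sex, age, race), traditional risk factors (smoking, diabetes, hypertension, obesity" and ending with the ApoB/ApoA1 ratio and the polygenic risk score (PRS). Centre, region, education and income are not on the list, although the Introduction names low education among the modifiable risk factors. For variables with a significant raised OR, an "attributable risk estimate will be calculated for the genetic component (PRS) and other covariables".
- **Quantitative variables and statistical analysis** says that "univariate and multiple unconditional logistic regression analyses will be conducted", with a univariate p < 0.20 screen and then backward elimination. Covariates that the investigator regards as confounders may now and then be forced into the final model; none is named.
- **Bias control** relies on eligibility, site training, adjudication, monitoring, a core laboratory and multivariable adjustment. It does not mention centre.

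**The concern.** The recruitment rule balances cases and controls overall on sex and age. One centre that enrols mostly cases and another that enrols mostly controls would both comply. The stated model then pools all centres. Any exposure whose prevalence, or whose recording, differs between centres can become associated with case status through the recruitment mix alone. Smoking, diet, alcohol, physical activity and psychosocial factors are the obvious candidates in a country-wide study.

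This bears on the study's main output. The Introduction makes the attributable fraction of the genetic profile, after adjustment for modifiable factors, the aim. The Variables section attaches an attributable risk to each variable with a significant raised OR, so a site-driven OR above 1 would receive a PAR directly. A site-driven shift the other way could hide a real factor and deny it one.

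**Working it through.** **1. The plan's own figure.** Inputs from Sample size calculation: OR 1.3, allele frequency 10%, dominant model, prevalence 10%, power 90%, two-sided α 0.05. Carrier frequency = 1 − 0.9² = 0.19. With baseline risk solved to give 10% prevalence, carriers are 18.57% of controls and 22.87% of cases. A likelihood-ratio calculation gives 1,866.7, i.e. 1,867 per group; a two-proportion formula gives 1,868. Power at 1,867 is 0.900. The stated 1,867 reproduces. It contains no centre or region element and is not in dispute.

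**2. Illustration of confounding by place.** The documents give neither site yields nor exposure by site, so these inputs are assumptions: two equal-sized groups of centres, exposure prevalence 25% and 15%, true OR 1, 1,867 cases and 1,867 controls, no other covariates. Let f be the share of all cases from the 25% group, with that group supplying 1 − f of the controls.

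- Exposure in cases: p₁ = 0.25f + 0.15(1 − f)
- Exposure in controls: p₀ = 0.25(1 − f) + 0.15f
- OR = [p₁/(1 − p₁)] / [p₀/(1 − p₀)]
- PAR = p₁(OR − 1)/OR
- z = (p₁ − p₀)/√{[p₁(1 − p₁) + p₀(1 − p₀)]/1,867}

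| f | Case:control in the two groups | p₁ | p₀ | Pooled OR | PAR | z | 5% test rejects |
|---|---|---|---|---|---|---|---|
| 0.5 | 1:1 and 1:1 | 0.20 | 0.20 | 1.00 | 0 | 0 | 5% |
| 0.6 | 1.5:1 and 1:1.5 | 0.21 | 0.19 | 1.13 | 2.5% | 1.53 | 33% |
| 0.7 | 2.3:1 and 1:2.3 | 0.22 | 0.18 | 1.28 | 4.9% | 3.06 | 86% |

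With the mix reversed, the ORs are 1/1.133 = 0.88 and 1/1.285 = 0.78.

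**3. Sensitivity to the assumed gap.** At 2:1 against 1:2, the pooled OR is 1.23 (PAR 4.1%) for exposure 25% and 15%, and 1.52 (PAR 8.0%) for 30% and 10%. With equal exposure in both groups there is no bias at any mix.

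**4. A factor with a real effect.** With true OR 2 and the 60/40 mix, exposure in cases is 0.6 × 0.40 + 0.4 × 0.261 = 0.344. The pooled OR is 2.24 and the PAR 0.344 × 1.24/2.24 = 19.1%, against 0.344 × 1/2 = 17.2% with the true OR. At an equal mix the pooled OR is 1.97, a slight attenuation.

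**5. Imbalance that is not aligned with exposure.** Step 2 assumes that case-heavy centres are also the high-exposure ones. A simulation of 50 centres let case share and exposure vary independently (mean prevalence 20%, SD 8 points, true OR 1). The unstratified test rejected about 6% of the time when site case shares ran from 35% to 65%. It rejected up to about 16% when they ran from 10% to 90%; that upper figure depends on how centre sizes and shares are drawn, and equal-sized centres give a lower one. The centre-stratified test stayed at about 5% throughout. Unaligned imbalance does modest harm, aligned imbalance more, and conditioning on centre removes both.

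**The case against.** Much can be said on the other side.

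- **Controls are linked to place.** Patient controls come from hospital and healthy controls from the same community, so a local 1:1 is a natural reading. This stands in part: the text links where controls are found to place, but not how many are enrolled per case.
- **Centre is not ruled out.** The clause on forced-in confounders would allow it. That stands, so the model cannot be said to exclude centre. But a design variable is then left to discretion, after the data are seen.
- **The full protocol is in a supplement that is not shown** and may set site quotas or a centre term. That is possible. The point rests on what the article does state: the recruitment rule, the covariate list, the model type and the selection method.
- **Recording differences are partly handled** by site training, monitoring and the core laboratory. This stands for biochemistry, and less fully for self-reported behaviour.
- **The example is chosen.** It is; the 70/30 mix is a marked imbalance with no covariate adjustment.

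Three stronger readings are tempting, and the article does not support them. A reader might take the reason given for 50 centres as a promise of confounder control that the analysis then breaks. It can equally describe coverage, in line with the call in the Introduction for geographic representation, so no contradiction is established. A reader might take the limitation that "assuring equality of individuals allocation based on geographic parameters is challenging" as an admission of unequal case:control ratios. It follows a remark on population density and socioeconomic disparity, and most naturally concerns how the sample is spread over the country. Finally, a reader might set the illustrative OR of 1.28 beside the OR of 1.3 used for sample size. That value was set for genetics and is no benchmark for modifiable factors.

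**Conclusion.** The point holds as a conditional one. The article ties 1:1 recruitment to sex and age only, and its stated model has no prespecified centre or region term. If case:control yield and exposure (or its recording) both vary between the 50 centres beyond what the listed covariates explain, the ORs can be confounded by place, and with them the PARs drawn from significant ORs. It is not shown that this has happened or will happen.

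The size cannot be derived from the documents. Under the assumed 25% and 15% exposure and a true OR of 1, it runs from nil (equal mix) through OR 1.13 and PAR 2.5% (60/40) to OR 1.28 and PAR 4.9% (70/30). The sample size is unaffected. Because conditioning on centre is cheap and protects against the problem whether or not it arises, the sponsor should prespecify it.

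**What to change.** - **Analysis.** Condition on centre in the primary models, by conditional logistic regression stratified on centre or by centre fixed effects. If a random intercept is preferred, add centre-mean exposure terms, since a plain random intercept does not fully remove between-centre confounding when exposure is correlated with centre.
- **Selection.** Keep centre out of the p < 0.20 screen and backward elimination, and do not leave it to the discretionary clause.
- **Attributable risk.** Use the centre-conditioned ORs. The formula in the working needs only the adjusted OR and the exposure prevalence in cases, so conditioning does not stand in its way.
- **Recruitment.** For what remains, pace control enrolment to cases within each centre, keeping the sex and age balance, and monitor the counts centrally.

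**Cost.** No new participants or assays. The average centre has 3,734/50 ≈ 75 participants (1,867/50 ≈ 37 cases), so conditioning is feasible, with some loss of precision where a centre has few cases or few controls. A centre with only cases or only controls contributes nothing to a centre-conditioned analysis; pool such centres by region, or report them in a sensitivity analysis. Recruitment began in July 2022, so the recruitment instruction can only be partial, and the analytic change carries most of the benefit.

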### Sample size calculation

We applied the following statistical assumptions: odds ratio for genetics was set at 1.3, allele frequency of 10%, inheritance model was dominant (since the presence of only one polymorphic allele is required to the risk calculation), the prevalence of CVD in the general population of 10%, statistical power of 90%, type I error rate (α) of 0.05, 2-sided significance tests, resulting in a sample of 1,867 cases and 1,867 controls. Sample size calculation was performed using Quanto Software Version 1.2.4.

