## Abstract

Atherosclerotic Cardiovascular Disease (ASCVD) represents the leading cause of death worldwide, and individual screening should be based on behavioral, metabolic, and genetic profile derived from data collected in large population-based studies. Due to the polygenic nature of ASCVD, we aimed to assess the association of genomics with ASCVD risk and its impact on the occurrence of acute myocardial infarction, stroke, or peripheral artery thrombotic-ischemic events at population level. CardioVascular Genes (CV-GENES) is a nationwide, multicenter, 1:1 case-control study of 3,734 patients in Brazil. Inclusion criterion for cases is the first occurrence of one of the ASCVD events. Individuals without known ASCVD will be eligible as controls. A core lab will perform the genetic analyses through low-pass whole genome sequencing and whole exome sequencing. In order to estimate the independent association between genetic polymorphisms and ASCVD, a polygenic risk score (PRS) will be built through a hybrid approach including effect size of each Single Nucleotide Polymorphism (SNP), number of effect alleles observed, sample ploidy, total number of SNPs included in the PRS, and number of non-missing SNPs in the sample. In addition, the presence of pathogenic or likely pathogenic variants will be screened in 8 genes (*ABCG5*, *ABCG8*, *APOB*, *APOE*, *LDLR*, *LDLRAP1*, *LIPA*, *PCSK9*) associated with atherosclerosis. Multiple logistic regression will be applied to estimate adjusted odds ratios (OR) and 95% confidence intervals (CI), and population attributable risks will be calculated.

**Clinical trial registration:** This study is registered in clinicaltrials.gov (NCT05515653).

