#### Estimation of population attributable risk

To characterize the study population, categorical variables will be described as counts and proportions and compared with Pearson’s chi-square test or with Fisher’s exact test [41]. Normally and asymmetrically distributed quantitative variables will be expressed as mean (standard deviation) or median (interquartile range), respectively [42]. Normality will be assessed by visually inspecting histograms and applying normality tests, if appropriate [43, 44]. Comparison of these continuous type variables will be carried out with Student’s t test for independent samples or Mann-Whitney test for non-parametric distribution [41].

All statistical analyses will follow the complete case analysis principle. All hypothesis tests will be 2-sided and p-value<0.05 considered statistically significant. Statistical data analysis will be conducted with SAS 9.4 (SAS Institute, Cary, NC).

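### The stated 90% power belongs to one dominant variant with nobody excluded, not to the planned polygenic-score analysis on a complete-case sample that changes between models

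*Protocol article*

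**What the plan says.** Under Sample size calculation, the protocol article assumes "odds ratio for genetics was set at 1.3, allele frequency of 10%, inheritance model was dominant". It justifies the dominant model "since the presence of only one polymorphic allele is required to the risk calculation". The other inputs are a disease prevalence of 10%, power of 90%, and "type I error rate (α) of 0.05, 2-sided significance tests". The result is 1,867 cases and 1,867 controls. The Abstract gives a total of 3,734.

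The Abstract describes a different exposure: a PRS "including effect size of each Single Nucleotide Polymorphism (SNP), number of effect alleles observed, sample ploidy" and further terms. The Variables section puts this score into multiple logistic models with demographic and traditional risk factors, and derives an attributable risk for it when its odds ratio is significant.

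Two rules then fix who is analysed. Under Estimation of population attributable risk: "All statistical analyses will follow the complete case analysis principle". Under Quantitative variables and statistical analysis, backward elimination "allows the sample size to adjust and always uses the maximum available sample as the number of variables in the model drops".

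**The concern.** A power statement should refer to the contrast that will be reported and to the people who will be in the model. Here neither matches. A score that sums weighted allele counts over many SNPs has no single allele frequency and no dominant inheritance model, so the inputs do not parameterise it. The total is exactly twice the calculated group size, while any participant with a missing covariate drops out of the models containing that covariate.

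The changing-sample rule is a separate weakness, and the article presents it as an advantage. If the sample grows when a covariate leaves, successive models are fitted to different people. A coefficient may then move because the sample changed rather than because a confounder was removed, and likelihood comparisons between steps are not valid. Because attributable risks are calculated only for variables with a significant odds ratio, this instability can reach the study's main output.

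**Working it through.** **Inputs from the document.** Odds ratio 1.3; allele frequency 0.10; dominant model; prevalence 0.10; power 0.90; two-sided alpha 0.05; 1:1 recruitment; unconditional logistic regression.

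**Step 1: reproduce the stated size.**
- Carrier frequency under Hardy-Weinberg: 1 − 0.9² = 0.19.
- Baseline odds b solve 0.81·b/(1+b) + 0.19·1.3b/(1+1.3b) = 0.10, giving b = 0.10525. Risk in carriers is 1.3b/(1+1.3b) = 0.12035.
- Carriers among cases: 0.19 × 0.12035/0.10 = 22.87%. Among controls: 0.19 × 0.87965/0.90 = 18.57%.
- Likelihood-ratio noncentrality per case plus control, with mean carrier frequency p̄ = 0.2072: λ = 2·Σ p·ln(p/p̄) over carriers and non-carriers in both groups = 0.005629.
- Required noncentrality: (1.960 + 1.282)² = 10.507.
- n per group = 10.507/0.005629 = 1,866.7, so **1,867**. Power at 1,867 is 90.0%.

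The matched-pair version gives 1,870. The stated figure is therefore the unmatched one: 1,867 cases and 1,867 controls, not 1,867 pairs. This agrees with the unconditional model.

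**Step 2: allowance for missing data.** 2 × 1,867 = 3,734, the full recruitment target, so nothing is added.

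**Step 3: the stated test after exclusions.** Power = Φ(√(n·λ) − 1.960), with n = 1,867 × (1 − loss). The article gives no missing-data rate, so the losses are assumptions, taken as equal in both groups. The last column is 1,867/(1 − loss), rounded up.

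| Assumed loss | n per group | Power | Recruits per group to keep 1,867 |
|---|---|---|---|
| 0% | 1,867 | 90.0% | 1,867 |
| 5% | 1,774 | 88.5% | 1,966 |
| 10% | 1,680 | 86.8% | 2,075 |
| 20% | 1,494 | 82.6% | 2,334 |
| 30% | 1,307 | 77.4% | 2,668 |

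**Step 4: the PRS.** For a standardised continuous score, unadjusted, the smallest odds ratio per SD with 90% power is exp(3.2415 × √(2/n)).
- n = 1,867: exp(3.2415 × 0.03273) = **1.112**
- 20% loss, n = 1,494: exp(3.2415 × 0.03659) = **1.126**
- 40% loss, n = 1,120: exp(3.2415 × 0.04226) = **1.147**

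Power at 1,867 per group is Φ(ln(OR)/√(2/n) − 1.960): 83% at OR 1.10 per SD, 99% at 1.15, and above 99.9% at 1.20. The article states no PRS effect size, so no single power figure can replace the 90%.

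**Step 5: the changing sample.** No arithmetic is needed. Complete-case analysis together with a sample that expands as variables leave means that two adjacent backward steps share the same participants only if the removed covariate had no missing value beyond those already excluded by the remaining ones.

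**The case against.** The strongest reply is that the mismatch does no demonstrated harm. The sum is right. Seen purely as statistics, it describes a binary exposure present in about 19% of controls at odds ratio 1.3. A PRS contrast of the top fifth against the rest at that odds ratio would have about 91% power with the same numbers, and the plan allows quantitative covariates to be categorised. The analysis section also speaks of genetic polymorphisms, so a single-variant test is not foreign to the plan, and univariate regressions lose nobody for missing covariates. Much of this stands. It means the sample size need not be wrong, but it does not make the stated 90% a statement about the PRS in an adjusted model.

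A reader might go further and infer that the study is underpowered. The document does not support that: Step 4 shows 90% power at modest PRS effects even after heavy loss.

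A reader might also apply a multiplicity penalty for many SNPs, a genome-wide threshold, or a power calculation for rare pathogenic carriers. None of these is a stated test. The SNP and locus counts in the Discussion come from the literature, the score uses only SNPs already associated with risk, and the eight genes are described as screened, with no hypothesis test given.

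Finally, a reader might claim that the complete-case odds ratios will be biased. That depends on how missingness relates to case status and exposure together, and the article says nothing on this. How many participants will be lost is equally unknown. Multiplying separate missing rates across all the covariates would assume independence and that every covariate enters the model, whereas missing data tend to cluster and selection removes variables.

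**Conclusion.** The point holds as a mismatch between the power basis and the planned analysis, together with a poor rule on the analysis sample. It is not an arithmetic error and not evidence of inadequate power. The 90% is correct for one prespecified dominant variant at allele frequency 10% and odds ratio 1.3, tested once, unadjusted, with complete data.

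For the PRS, the same recruitment gives 90% power at an odds ratio per SD of about 1.11, rising to 1.13 and 1.15 at 20% and 40% loss. These values assume a standardised score, equal loss in cases and controls, and no covariate adjustment. Whether the 90% understates or overstates the power for the PRS depends on an effect size that the article does not give; the crossover is near 1.11 per SD with complete data.

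The changing-sample rule should go whatever the power, because it makes successive models non-comparable. This should be corrected; it does not invalidate the study.

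**What to change.** 1. **Sample size calculation.** Restate it as the PRS odds ratio per SD detectable with 90% power by 1,867 cases and 1,867 controls (not pairs). Label the figure unadjusted and show it over a range of assumed losses, for example 1.11, 1.13 and 1.15 at 0%, 20% and 40%. Add that the 90% at odds ratio 1.3 applies only to a single prespecified common variant with complete data, and that other SNP-level and monogenic associations are exploratory.
2. **Quantitative variables and statistical analysis.** Delete the changing-sample rule. Carry out variable selection and fit the final models on one fixed analysis set. Impute missing covariates by multiple imputation, with case status, PRS, age, sex and centre in the imputation model.
3. **Estimation of population attributable risk.** Replace the complete-case rule with the above and keep complete-case analysis as a sensitivity analysis.

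The cost is rewording and some extra analysis work in the software already named, with no extra participants. Imputation relies on a missing-at-random assumption, which is one reason to report the complete-case results beside it.
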